The following primary objectives were selected: First, to evaluate the efficacy of NBO in reducing anemia in CRC patients undergoing chemotherapy by measuring markers of erythropoiesis, such as EPO levels, HIF-1α, and complete blood counts. Second, to evaluate the effect of NBO on reducing oxidative stress and improving patients’ cognitive and emotional functions by analyzing levels of cortisol, GABA, dopamine, and other indicators of allostatic load. Third, to analyze the effects of NBO on immune system parameters and reduction in oxidative stress by evaluating a panel of 24 serum cytokines and TNFα levels. Fourth, to identify genetic markers of response to NBO therapy by analyzing the secretome to investigate molecular changes and profiles related to immune function and response to treatment. The effects of NBO on improving patients’ cognitive and emotional functions were quantified simultaneously in the same clinical specimen. In turn, a secondary objective is to assess the impact of NBO on patient-reported outcome measures (PROMs) using standardized tools such as the Perceived Stress Questionnaire (PSQ), Hospital Anxiety and Depression Scale (HADS), and Euro-Quality of Life Questionnaire (EQ-5D).

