#### 2.8.3. IMMUNO and GENETICS Packages

We will analyze a comprehensive cytokine panel (24-plex or 45-plex) to capture the full spectrum of immune modulation in CRC patients. This panel includes pro-inflammatory (e.g., TNF-α, IL-1β, IL-6), anti-inflammatory (e.g., IL-10), chemotactic (e.g., MCP-1, MIP-1α/β), and growth factors (e.g., VEGF, PDGF) that are collectively relevant for tumor progression, immune cell recruitment, and therapy response in CRC. Multiplex immunoassay technology (e.g., Luminex or similar platforms) will be employed to simultaneously measure these cytokines in a single sample, which enhances throughput, reduces sample volume requirements, and minimizes technical variability compared with individual ELISAs.

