### 2.10. Statistical Analysis

Descriptive statistics will be used to summarize study results. Central tendency and dispersion measures will be calculated using parametric or non-parametric methods depending on data distributions. Repeated measures data (V1, V2, V3, V4, and V5) will include ordinal and interval data analyzed with repeated measures ANOVA (parametric) or the Friedman test (non-parametric). Data normality will be verified with the Shapiro–Wilk test. Depending on the distribution, data will be presented as means with standard deviations (parametric) or medians with interquartile ranges (IQRs) (non-parametric). Comparisons between baseline (V1) and follow-up (V4, V5) visits will use the Wilcoxon signed-rank test for paired variables and the Friedman test for multiple comparisons. Post hoc analysis (for significant Friedman tests) will apply Wilcoxon tests with Bonferroni corrections. For between-group comparisons (intervention vs. control), the Mann–Whitney U test will be used.

A comprehensive sample size analysis was conducted to ensure that the study is adequately powered to detect a statistically significant effect of NBO therapy on erythropoiesis stimulation among patients undergoing chemotherapy. The primary endpoint considered was the assumed 40% difference between the active NBO group and the placebo group in the primary outcome measure related to erythropoiesis, such as erythropoietin (EPO) levels. To achieve adequate statistical power, the analysis aimed for 80% power (β = 0.20), indicating a high probability of detecting a true effect if it exists, at a significance level of 5% (α = 0.05), which is the conventional threshold for statistical significance. Effect size estimation was based on Cohen’s (1992) [41] classification, where a small effect size ranges from 0.1 to 0.29, a medium effect size ranges from 0.3 to 0.49, and a large effect size ranges from 0.5 to 1. An effect size corresponding to a medium to large effect was anticipated due to the expected impact of NBO on erythropoiesis.

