For the CRC groups (Groups 1 and 2), it was determined that 127 patients per group are required. This accounts for a potential 30% dropout rate, ensuring that the final sample maintains the desired power and accounting for the challenges associated with patient retention over the study period. The sample size calculations were performed using G*Power software (version 3.1.9.7 or the latest version). The parameters used in the calculation included the expected effect size (d), calculated based on the anticipated difference and standard deviation from pilot studies or the existing literature. An allocation ratio (N2/N1) of 1 was used, indicating equal allocation between the active NBO and placebo groups. The test family selected was *t*-tests for means between two independent groups, focusing on the difference between two independent means.

Assumptions made during the calculation included a confidence level of 95% and the use of a two-tailed test, considering the possibility of the effect in both directions. It was also assumed that the variability in outcome measures would be similar across groups, which is important for the validity of the statistical tests used.

The rationale for this sample size is to ensure that the study is sufficiently powered to detect clinically meaningful differences between the active NBO and placebo groups in the primary outcome measures. By accounting for a 30% dropout rate, the study design acknowledges the realities of clinical research involving patients undergoing chemotherapy, who may experience side effects or other factors leading to withdrawal from the study.

An interim analysis will be conducted after 50% of participants have completed the study. The research team will assess data on safety and efficacy trends during this analysis. Based on interim findings, sample size adjustments may be considered, adhering to statistical guidelines to control for Type I error inflation and ensuring the integrity of the study.

Statistical analyses will be performed using software such as SPSS (version 26 or later) and R (version 4.0 or later) with appropriate packages. Supplemental tools like SAS 9.4 M8 or Stata 19 may be used if needed. Data management will involve entering data into a secure database with validation checks to ensure accuracy. Data cleaning procedures will be implemented prior to analysis to address any inconsistencies or errors.

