Handling of missing data is an important aspect of the analysis plan. An intention-to-treat (ITT) analysis will be conducted, including all randomized patients in the analysis according to their assigned groups. Missing data will be handled using appropriate statistical methods such as multiple imputation or last observation carried forward (LOCF), depending on the nature and extent of the missing data. Additionally, a per-protocol (PP) analysis will be conducted as a secondary analysis, including only patients who completed the study without major protocol deviations, to assess the robustness of the findings.

Adjustment for multiple comparisons will involve the use of Bonferroni correction or other suitable methods when conducting multiple statistical tests. This approach helps control the overall Type I error rate, reducing the likelihood of false-positive findings due to multiple tests. Sensitivity analyses will also be performed to assess the robustness of the results under different assumptions and statistical models, providing additional confidence in the study conclusions.

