## 3. Results

The results of this study will focus on primary outcomes, including changes in erythropoietin (EPO) levels, oxidative stress markers, and immune function parameters, comparing pre- and post-intervention values between the active NBO and placebo NBO groups. Secondary outcomes will assess improvements in patient-reported outcome measures (PROMs), stress reduction, and psychological well-being based on standardized assessment tools, including the Perceived Stress Questionnaire (PSQ), Hospital Anxiety and Depression Scale (HADS), and EuroQol-5D (EQ-5D).

We anticipate that participants in the active NBO group will exhibit greater erythropoiesis stimulation, lower inflammatory cytokine levels, and improved stress adaptation compared with the placebo group. Furthermore, this study may provide insights into the long-term benefits of NBO therapy by analyzing patient outcomes at 3- and 6-months post-intervention.

Patient recruitment in the clinical setting is expected to be completed by 2030. Screening for eligible participants, based on the predefined inclusion and exclusion criteria, will be finalized in 2028. Informed consent will be obtained from all eligible study participants before enrollment, with the first participant scheduled to be enrolled in March 2026. Data analysis is projected to begin in June 2030, followed by the publication of primary and final results.

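### Several objectives and whole biomarker packages are called primary, but the 80% power holds for one erythropoiesis test at 0.05 and not for the primary set as written

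*Protocol article*

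**What the plan says.** The article describes what is primary in four ways.

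- **Introduction (last paragraph).** "The following primary objectives were selected", followed by four numbered objectives: anaemia and erythropoiesis; oxidative stress with cognitive and emotional function; immune parameters; and genetic markers of response.
- **Section 2.8, Primary Outcomes.** The full ANEMIA, STRESS and IMMUNO/GENETICS packages. The immune panel is left open: "We will analyze a comprehensive cytokine panel (24-plex or 45-plex". The Introduction speaks of 24 cytokines and TNFα.
- **Section 3, Results.** Three groups: "primary outcomes, including changes in erythropoietin (EPO) levels, oxidative stress markers, and immune function parameters".
- **Section 2.10, sample size.** One measure related to erythropoiesis, for which EPO is only an example.

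The sizing in 2.10 is for a single comparison of two independent means: "the analysis aimed for 80% power (β = 0.20"), "at a significance level of 5% (α = 0.05"), with "the use of a two-tailed test". It gives 127 per group including 30% dropout. The same section then says that this size is sufficient for the primary outcome measures, in the plural, and later that "Adjustment for multiple comparisons will involve the use of Bonferroni correction or other suitable methods when conducting multiple statistical tests". It does not say which tests form the family to be adjusted.

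**The concern.** A sample size computed for one test at 0.05 gives its stated power for that test only. If several outcomes are primary and the significance level is divided among them, each is tested at a stricter level and its power falls. If the level is not divided across all of them, the chance of a false primary finding exceeds 5%. The article makes many outcomes primary, promises an adjustment, and keeps the unadjusted 80% as if it covered all of them.

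At stake is the definition of success. A reader of the final report could not tell from this text whether a significant cytokine or cortisol result counts as a positive trial, or which result the 80% referred to.

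**Working it through.** **Inputs.** From 2.10: two-sided alpha 0.05, power 0.80, 1:1 allocation, two-sample t-test, 127 per group, 30% dropout. The article states no numerical d and no SD, so 127 cannot be derived forward from its own inputs. I work backwards.

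**Step 1, the effect size implied by 127.**
- Evaluable per arm: 127 × 0.70 = 88.9, about 89.
- With 89 per arm, the t-test has 80% power at two-sided 0.05 when d = 0.422.
- Check by the normal formula: n = 2(1.960 + 0.842)²/0.42² = 89.0, and 89/0.70 = 127.1. This agrees with the stated size.

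The value d = 0.42 is an assumption, but the results barely depend on it. Taking 88, 97, 98 or 127 as the sample that has 80% power changes the t-based figures below by less than half a percentage point.

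**Step 2, how many primary variables.** Blood morphology and the lipid panel are counted as one each.
- ANEMIA, 17: EPO, HIF-1α, blood morphology, creatinine, eGFR, ALT, AST, glucose, insulin, lipid panel, TIBC, iron, ferritin, B12, albumin, CRP, reticulocytes.
- STRESS, 14, with CRP not counted twice: ROS, cortisol, GABA, dopamine, serotonin, fibrinogen, HbA1c, DHEA-S, SBP, DBP, heart rate, BMI, BSA, WHR.
- IMMUNO: 24 or 45 cytokines.

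The total is 17 + 14 + 24 = 55, or 17 + 14 + 45 = 76. If the six separate allostatic-load components (fibrinogen, HbA1c, DHEA-S, SBP, DBP, heart rate) become one score, STRESS falls to 9 and the total to 50. If eGFR is treated as derived from creatinine, the total is 49. GENETICS is not counted.

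**Step 3, power per endpoint if Bonferroni spans the set.** By the normal approximation, power = Φ(2.802 − z), where z is the two-sided critical value at 0.05/m. For m = 4, z at 0.0125 is 2.498 and Φ(0.304) = 0.619. The exact t-test figures at 89 per arm and d = 0.422 are:

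| Tests m | Basis | Alpha per test | Power |
|---|---|---|---|
| 1 | as sized | 0.05 | 80% |
| 3 | outcome groups in Results | 0.0167 | 65.5% |
| 4 | one test per objective (assumption) | 0.0125 | 61.6% |
| 50 | packages, 24 cytokines, allostatic load as one | 0.0010 | 30.3% |
| 55 | packages, 24 cytokines | 0.00091 | 29.3% |
| 76 | packages, 45 cytokines | 0.00066 | 26.2% |

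The d detectable with 80% power rises from 0.42 to 0.63 with 55 tests. Restoring 80% at d = 0.422 would need 127 evaluable per arm for four tests (127/0.70, so 182 randomised) or 197 for 55 tests (197/0.70, so 282 randomised).

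**Step 4, false positives if Bonferroni is applied only within each package.** Each of three packages is held to at most 0.05.
- Upper bound: 3 × 0.05 = 15%.
- For independent tests: 1 − (1 − 0.05/17)^17 × (1 − 0.05/14)^14 × (1 − 0.05/24)^24 = 0.139, about 14%.

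**The case against.** The best defence is that 2.10 does not commit to Bonferroni; it also allows other suitable methods. A fixed sequence that tests EPO first would keep the full 80% for EPO and still control the overall error. That stands. The losses in step 3 follow only if Bonferroni spans the primary set, so a reader who infers that the statements are flatly incompatible goes too far. But no sequence or family is fixed, and no such method turns the single-test 80% into 80% for every primary measure.

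Other limits also stand:

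- **The count.** Fifty-five is not a floor. Several items, such as kidney and liver markers and anthropometry, read as much like profiling as efficacy tests. Power differs little between 50 and 55 tests.
- **Four tests.** The fourth objective, finding genetic markers of response, is not an ordinary active-versus-placebo test. The three groups in the Results section are the better small-family reading.
- **The effect size.** The article assumes an effect only for erythropoiesis. Applying d = 0.42 to every marker is an illustration.
- **The visit.** One might infer that the article gives no hint of a primary time point. It does: Results compares pre- and post-intervention values, and 2.7 and Table 1 label V1 as pre-test and V3 as post-test.

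One could add that multiplicity details belong in an analysis plan. The mechanics do. What is primary and what the power covers are stated here, and the statements disagree.

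**Conclusion.** The concern holds in this form: the primary set is inconsistent across the Introduction, 2.8, 2.10 and Results, and the stated 80% applies to one endpoint only. If Bonferroni spans the set, per-endpoint power is about 66% for three tests, 62% for four, 29–30% for roughly 50–55 variables and 26% for 76. If it is applied within three packages, the overall false-positive chance is about 14% rather than 5%. The power figures rest on 89 evaluable per arm and the back-solved d; the 14% assumes independent tests.

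A reader might also infer that some primary outcome is almost certain to be significant by chance. Fifty-five independent tests at 0.05 with no correction would give 1 − 0.95^55 = 94%, but 2.10 promises an adjustment, so the documents do not support that reading.

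This should be settled before enrolment, because the trial's definition of success depends on it.

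**What to change.** - Name one erythropoiesis variable, active versus placebo, at V3, as the single primary endpoint, tested at two-sided 0.05. This matches the sample size already computed.
- Make the remaining ANEMIA, STRESS and IMMUNO variables secondary with a stated multiplicity method, for example Benjamini–Hochberg within each package. Make GENETICS exploratory.
- Choose either the 24-plex or the 45-plex panel.
- Limit the 80% power statement in 2.10 to the primary endpoint.
- Align the Introduction, 2.8, 2.10 and Results.

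The cost is wording, and bringing the registration into line where needed, before the first enrolment planned for March 2026. The size of 127 per group need not change on this account. The downside is that STRESS and IMMUNO results can no longer be called primary.

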### 2.11. Patient Withdrawal

Participants may be withdrawn from the study under specific conditions to ensure safety, data integrity, and adherence to protocol requirements. Voluntary withdrawal allows participants to withdraw consent at any time without penalty or loss of benefits, and they are not required to provide a reason. Medical reasons for withdrawal may arise if the investigator determines that continued participation is not in the patient’s best medical interest due to medical conditions or adverse events that pose a risk. Eligibility non-compliance may lead to withdrawal if post-enrollment evaluation reveals that a participant does not meet inclusion criteria or meets exclusion criteria. Protocol non-adherence, such as a failure to follow study procedures, repeated absences from scheduled visits, or non-compliance affecting data integrity, may result in removal from the study. Pregnancy during the study requires immediate withdrawal for safety reasons. The principal investigator also retains the discretion to withdraw any participant if their continued participation is deemed unsafe or not in their best interest.

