### 2.4. Eligibility Criteria

Inclusion criteria: (1) age between 18 and 80 years (participants must be adults); (2) diagnosed with CRC (stage II–IV, scheduled for standard chemotherapy (for the study and control groups); (3) baseline hemoglobin levels above 10 g/dL; (4) no concurrent hematologic malignancies; (5) an eastern Cooperative Oncology Group (ECOG) performance status of 0–2 (ensuring that participants are ambulatory and capable of self-care); (6) a life expectancy of at least 12 months (participants are expected to survive for the duration of the study); (7) the ability and a willingness to comply with all study procedures and schedules (including NBO therapy sessions and follow-up visits); (8) adequate organ function as determined by laboratory tests (liver function tests (ALT, AST) and renal function tests (serum creatinine, eGFR)); (9) women of childbearing potential must have had a negative pregnancy test prior to enrollment and agreed to use effective contraception during the study (to ensure safety for potential pregnancies); and (10) written informed consent was obtained prior to any study-related procedures (participants must understand and agree to all aspects of the study).

Exclusion criteria: (1) age under 18 years or over 80 years; (2) severe cardiovascular or respiratory conditions (e.g., unstable angina, recent myocardial infarction, advanced COPD); (3) severe anemia (hemoglobin < 10 g/dL) or any hemolytic disorder that could confound study outcomes; (4) uncontrolled diabetes mellitus (e.g., HbA1c > 8.0% or poor glycemic control requiring frequent hospitalizations); (5) pregnancy or breastfeeding; (6) severe infection or immunocompromised status unrelated to cancer (e.g., advanced HIV infection); (7) current psychiatric or neurological disorders that could interfere with study participation; (8) participation in other investigational therapies within the last 30 days; (9) a lack of written informed consent for study participation; (10) autoimmune or inflammatory conditions (e.g., lupus, rheumatoid arthritis on immunosuppressive therapy) that significantly alter immune responses; and (11) the presence of any contraindication for NBO therapy (e.g., active bleeding, acute infections, inflammation of the optic nerve, epilepsy or seizures, uncontrolled diabetes as noted above, pneumothorax, emphysema, electronic implants).

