### 2.7. Research Plan

The patient assessment scheme contains six visits from V0 to V5 with subsequent analytical packages with a detailed explanation provided in Section 2.8. The patient assessment schedule consists of six visits, from V0 to V5, each including specific evaluations and interventions. The study will begin with V0 (prequalification/screening), where patient consent will be obtained, medical history will be collected, and baseline data will be recorded. V1 (randomization and pre-test visit) will involve the initial assessments, including anemia, stress, immune function, genetic markers, and patient-reported outcomes (PROMs). Following this, the first phase of the NBO intervention (sessions 1–5) will take place over five weeks. At V2 (midpoint evaluation), the same set of assessments will be repeated to track progress, followed by the second phase of the NBO intervention (sessions 6–10) conducted over the next five weeks. V3 (finalization and post-test visit) will mark the completion of the intervention, with a final round of primary and secondary outcome assessments. The study will then proceed with two follow-up visits: V4 (3 months post-NBO) and V5 (6 months post-NBO), where anemia, stress, immune function, genetic markers, and PROMs will be reassessed to evaluate the long-term effects of the intervention. Table 1 presents the research plan (Figure 1).

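### Section 2.11 lets randomized patients be taken out of the study for non-adherence or late-found ineligibility, with no option to stop NBO sessions and keep the V2–V5 assessments

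*Protocol article*

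**What the plan says.** Section 2.11 opens with the general rule: "Participants may be withdrawn from the study under specific conditions to ensure safety, data integrity, and adherence to protocol requirements". Two of the grounds that follow concern conduct and eligibility rather than safety:

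- Non-adherence, where "a failure to follow study procedures, repeated absences from scheduled visits, or non-compliance affecting data integrity, may result in removal from the study".
- Late-found ineligibility: "Eligibility non-compliance may lead to withdrawal if post-enrollment evaluation reveals that a participant does not meet inclusion criteria or meets exclusion criteria".

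The other grounds are withdrawn consent, medical reasons, the principal investigator's discretion, and pregnancy ("Pregnancy during the study requires immediate withdrawal for safety reasons"). The section gives no intermediate status in which sessions are stopped and visits kept, and no other section of the article supplies one.

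Section 2.10 promises an ITT analysis "including all randomized patients in the analysis according to their assigned groups". Gaps are to be filled by methods such as multiple imputation or LOCF. A secondary per-protocol analysis is restricted to patients who complete without major deviations, and sensitivity analyses are planned. The 30% dropout allowance is explained by reference to patients on chemotherapy, "who may experience side effects or other factors leading to withdrawal from the study".

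Section 2.7 schedules assessments at V2 to V5 for every randomized patient. At V4 and V5, three and six months after NBO, it describes visits "where anemia, stress, immune function, genetic markers, and PROMs will be reassessed to evaluate the long-term effects of the intervention".

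**The concern.** An ITT analysis is most convincing when outcomes are measured on everyone randomized, whether or not they kept to the intervention. A rule that takes poor adherers and late-found ineligible patients out of the study works against that. It turns outcomes that could have been observed into missing ones, by a decision made after randomization.

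Adherence can depend on how the patient is faring, so the resulting gaps may be informative. They may also differ by arm. Under sections 2.6.1 and 2.6.2 the arms differ in pressure (1500 against about 1000 hPa) and carbon dioxide (0.7–1.9% against about 0.03%) as well as oxygen, so tolerability and attendance could plausibly differ.

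The outcomes at stake are the primary laboratory packages of section 2.8 and the patient-reported measures of section 2.9, including the two late visits that carry the long-term question. Imputing them rests on assumptions that the trial's own data cannot test. Observed values need no such assumptions.

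**Working it through.** **1. The provisions side by side**

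| Ground (section 2.11) | Action named | Mandatory? | Does the action serve safety? | Handled elsewhere? |
|---|---|---|---|---|
| Non-adherence, repeated absences | Removal from the study | No | No | Per-protocol set, section 2.10 |
| Ineligibility found after enrollment | Withdrawal | No | Not as such; stopping sessions covers any risk from NBO | Per-protocol set, if a major deviation |
| Medical reasons, adverse events | Withdrawal | No | Yes | – |
| Pregnancy | Withdrawal | Yes | Yes | – |

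The first two rows are the problem. There, removal adds nothing that stopping sessions and the per-protocol set do not already achieve, and it costs outcome data.

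**2. What one removal costs**

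This reads removal as ending the remaining assessments.

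| Removed | Last possible observation | Visits lost | Value LOCF would use |
|---|---|---|---|
| Before V2 | V1 | V2–V5 (4) | V1, baseline |
| Between V2 and V3 | V2 | V3–V5 (3) | V2, mid-course |
| Between V3 and V4 | V3 | V4, V5 (2) | V3, end of sessions |
| Between V4 and V5 | V4 | V5 (1) | V4 |

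All sessions fall before V3, so removal while they are running loses three or four of the four post-randomization visits. LOCF would then stand a baseline or mid-course value in for an outcome six months after NBO. Removal for repeated absences has a further effect: a patient who misses V2 and V3 but could attend V4 and V5 goes from intermittently to permanently missing.

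**3. Scale**

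Inputs from section 2.10: 127 patients per arm and 30% dropout. The 127 is taken as stated. It cannot be reproduced directly because the article gives no numerical effect size or standard deviation, and this point does not depend on it.

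- Budgeted dropouts: 0.30 × 127 = 38.1, about 38 per arm.
- Scheduled post-randomization visits: 127 × 4 = 508 per arm.
- Visits lost: removed patients × 1 to removed patients × 4.

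The documents do not say what share of dropouts would leave through these decisions. The shares below are assumptions that show the range.

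| Assumed share of the 38 | Patients per arm | Visits lost | Percent of 508 |
|---|---|---|---|
| 10% | 3.8, about 4 | 4–16 | 0.8–3.1 |
| 25% | 9.5, about 10 | 10–40 | 2.0–7.9 |
| 50% | 19 | 19–76 | 3.7–15.0 |
| 100% (arithmetic ceiling) | 38 | 38–152 | 7.5–29.9 |

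The ceiling leaves no one who withdrew consent, so it is not a forecast. All rows overstate what the fix could recover, because some of these patients would have missed or declined the visits anyway. No bias can be computed: the documents say nothing about how removed patients would differ from the rest.

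**The case against.** The best case for the plan has several parts.

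- **The article never says outright that data collection ends.** This is true. But removal from the study ordinarily means it, and nothing shown keeps such patients in V2–V5. The full protocol may separate stopping treatment from leaving the study. If so, the published wording should say the same.
- **The grounds are discretionary, apart from pregnancy.** Investigators may keep patients in follow-up under the present text. This reduces the likely number, but leaves retention to individual judgment after randomization.
- **Repeated absentees are already not supplying data.** This holds in part: formal removal costs little for those who would never return, but it closes the door on those who would.
- **Blinding and sensitivity analyses protect the comparison.** Section 2.5 blinds clinical staff and data collectors, which limits arm-driven decisions. It does not prevent loss caused by a real difference in tolerability. Sensitivity analyses can probe imputation assumptions, but cannot recover unmeasured outcomes.

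A reader might also infer three stronger points that the documents do not support.

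- **That section 2.11 contradicts the ITT commitment.** It does not: all randomized patients can stay in the analysis with imputed values.
- **That missed NBO sessions alone are a stated ground for removal.** Inclusion criterion 7 in section 2.4 does count sessions among the procedures to be complied with, but it is an entry criterion. Section 2.11 does not name sessions among its examples.
- **That the medical and pregnancy provisions are defects of the same kind.** They are safety provisions, worded only as withdrawal. Pregnancy should be rare, given the negative test and contraception required at entry.

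**Conclusion.** The point stands in a limited form, as something that should be changed. For non-adherence and late-found ineligibility, section 2.11 permits a step that serves no evident safety purpose, duplicates what the per-protocol analysis already does, and can exchange measurable outcomes for imputed ones.

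This rests on two things: the ordinary meaning of leaving the study, and the absence from the article of any provision to continue assessments. The number of patients affected is unknown. The visit-loss percentages depend on assumed shares, and neither the size nor the direction of bias can be stated. It would go too far to call the ITT analysis invalid, or to quote the 30% ceiling as an expected loss.

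**What to change.** Amend section 2.11 to separate two statuses.

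1. **NBO sessions stopped, patient remains in the study.** Non-adherence and late-found ineligibility lead at most to this status and to exclusion from the per-protocol set. V2–V5 continue and the observed values enter the ITT analysis. For medical reasons and pregnancy, sessions stop at once as now, and V2–V5 continue where the assessments are safe and the patient consents.
2. **Withdrawn from the study.** This is reserved for patients who withdraw consent to follow-up, or for whom the assessments themselves are unsafe. A patient who only refuses further sessions is asked whether visits may continue.

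The cost is a short amendment plus attendance by patients off NBO at visits already scheduled for every randomized patient. On the arithmetic above that is at most 152 visits per arm for these two grounds, and fewer in practice because some will decline. No stated sample size or analysis changes. Keeping patients who are off NBO may make the ITT group difference smaller than under full exposure. That is the effect ITT is meant to estimate, and the per-protocol analysis remains for the other question. Section 3 plans first enrollment for March 2026. The change is best made before then, since missed visits cannot be recovered later.
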